## Abstract

Metabolic control is poor in East Africa for youth with type1 diabetes (T1D). Self-monitoring of blood glucose (SMBG) by fingerstick 2–3 times daily is routine care. This randomized controlled trial (RCT) will test the hypothesis that providing continuous glucose monitoring (CGM) to Ugandan youth with T1D will improve glucose time-in-range (TIR glucose 3.9–10.0 mmol/L) and be cost effective in this setting. Ugandan youth with T1D (*n* = 180, age 4–26 years) will be divided into four 12-month cohorts (August 2022–August 2027). Half will receive unblinded Freestyle Libre 2 Flash CGM for 12 months. For six months, control subjects received sufficient test strips for SMBG three times daily while wearing blinded Freestyle Libre Pro CGM (for endpoint assessment), and then they switch to unblinded CGM for six months. Everyone receives monthly diabetes education. The primary endpoints are as follows: (1) the six-month change from baseline in glucose TIR, unblinded CGM versus SMBG; (2) a cost analysis of CGM versus SMBG. The TIR hypothesis will be tested by linear mixed effects models. Cost analysis assumptions include direct material and indirect costs like hospitalizations, missed school/work, and diabetes complications. The study will inform T1D management guidelines in a low resource setting using evidence-based recommendations.

## 1. Introduction

Although the data are incomplete due to inconsistent reporting, the International Diabetes Federation (IDF) reported that in 2024 about 352,000 individuals with T1D were living in Africa, ~98,000 of whom (28%) were children [1]. The prevalence continues to rise as detection, reporting, and survival improve [1]. In Uganda, ~6000 children and young [1] adults now live with T1D [1].

Ugandan youth up to age 26 are followed monthly in dedicated diabetes clinics staffed by trained personnel, and receive adequate quantities of insulin, diabetes education, and 2–3 glucose test strips per day. This level of care is considered to be within the diabetes “intermediate care” tier [2]. Metabolic control is poor in this population, with extremes of both hypo- and hyperglycemia and average hemoglobin A1c (HbA1c) levels of ~11% (97 mmol/mol) [3]. Both acute and chronic life-threatening diabetes complications are common. Thus, the current level of T1D management is inadequate.

Glucose monitoring is an essential component of diabetes care, and more frequent monitoring is associated with lower HbA1c levels [4]. International T1D guidelines recommend SMBG at least 6–10 times per day [5,6]. GM is rapidly replacing SMBG as standard-of-care in high-resourced nations. It is associated with lower HbA1c levels, increased glucose TIR, and less hypoglycemia [7,8,9,10,11,12]. The American Diabetes Association recommends access to CGM from the outset of T1D diagnosis [6].

CGM is currently considered too expensive for low-resource settings. However, frequent glucose monitoring by any means is expensive, and CGM devices have been shown in high income countries to be cost effective compared to SMBG. A systematic review on the cost effectiveness of CGM in people with TID suggests CGM appears to be a cost-effective tool by reducing short- and long-term complications for individuals with type 1 diabetes [13]. Another study in Sweden showed benefit of Flash CGM over SMBG in hypoglycemia and health utility benefits, which may ultimately lead to economic benefit [14]. A 2020 US cost comparison found that flash glucose monitoring was equivalent in price to three times daily SMBG [15]. In addition to direct material costs, cost-benefit calculations consider avoidance of diabetic ketoacidosis (DKA) and severe hypoglycemia, preventing micro- and macrovascular complications, providing the opportunity to achieve normal life milestones (education, sports participation, employment, marriage, having children) and being able to expect normal longevity.

This protocol aims to determine whether CGM leads to significant improvement in diabetes metabolic control in Ugandan youth with T1D, and includes cost-benefit analysis by the Ugandan Ministry of Health since the economic realities of this technology may differ between low- and high-income settings. These data will help inform treatment decisions in Uganda and may be applicable to other low-resource countries. The study also provides an opportunity for the experienced Minnesota research team to train and mentor the Ugandan pediatric diabetes team in the conduct of RCTs, thus increasing local research capacity. The protocol follows the Standard Protocol Items Recommendations for Interventional Trials (SPIRIT) details in Table S1.

## 2. Methods

### 2.1. Study Methods Development

This study grew out of a long-standing clinical partnership between [name] at the University of Minnesota and [name] at Mulago Hospital, the Ugandan national referral hospital and the teaching hospital of Makerere University. In preparation, they performed a pilot study of 78 East African youths using a single, blinded CGM wear, to assess feasibility and participant acceptance of this technology and to generate data for sample size estimation [3]. While planning the current RCT, they considered several challenges and potential limitations that informed the ultimate approach, as outlined in Table A1. Goals important to the investigators included ensuring there was a true control group receiving standard SMBG care (with simultaneous blinded sensor wear for endpoint assessment), allowing every participant to experience unblinded CGM use (the control group crosses over to unblinded CGM after the first six months), and assessing the durability of CGM benefits beyond the six-month primary endpoint (the CGM group continues until 12 months).

### 2.2. Objectives

The primary objectives of this study are outlined as follows:To determine if patients’ ability to continuously observe interstitial glucose levels for six months using the Freestyle Libre 2 flash CGM device (Abbott Diabetes Care, Alameda, CA, USA) improves glucose TIR from baseline assessment. The change in glucose TIR while wearing the unblinded CGM will be compared to change in TIR in patients performing three times daily SMBG.To perform a cost analysis on flash glucose monitoring compared to three times daily SMBG, to determine whether this technology is cost effective in the setting of a less-resourced nation.

Secondary objectives are as follows: to assess the change-from-baseline impact of unblinded CGM on percent TIR at 12 months; percent time with glucose in hyper- and hypoglycemic ranges; glucose variability (coefficient of variation, CV); HbA1c; patient satisfaction, quality of life, and fear of hypoglycemia. There are also training objectives for the Ugandan research team and the Kampala diabetes community.

### 2.3. Overview, Study Design

This randomized, non-blinded, phase 4 clinical trial is programmed as follows. Subjects are assigned 1:1 to the CGM Group or the Control Group. Randomization is stratified by clinic and by age group (4–11, 12–18, and 19–26 years) with approximately equal numbers in each age group and of the two clinic locations. The random numbers were generated by the statistician using a central computer. At baseline, a 1–2 weeks initial assessment is performed where the ability to wear and return the sensor can be demonstrated, as an entry criterion for randomization. After this, 180 children and young adults with T1D will be randomized into the clinical trial in four 12-month cohorts of 45 patients each.

The study design is shown in Figure 1. Half of the subjects (*n* = 90, CGM Group) receive unblinded FreeStyle Libre 2 CGM for the entire 12 months. Half (*n* = 90, Control Group) are given sufficient test strips for three times daily SMBG months 1–6, while wearing blinded CGM for endpoint assessment. For months 7–12 they switch to unblinded CGM. The treatment group is expected to continuously modify their insulin dose and behaviors based on real-time, continuous availability of glucose data. The control group has no access to these data and will base their actions on SMBG measurement alone. For study data analysis, we will use unblinded sensor data from the treatment group and blinded sensor data from the control group that is obtained in the two weeks preceding each monthly visit; thus, the CGM data comparison period will be the same for both groups.

The investigators and the patients are not blinded to treatment arm as there is no practical way to do this. But they are blinded to the comparison data for CGM versus SMBG use until the study is completed. Table 1 lists the schedule of study assessments.

A baseline 1–2 weeks initial assessment will be performed where the ability to wear and return the CGM can be demonstrated as an entry criterion for study randomization. After this, 180 children and young adults with T1D will be randomized to a 12-month clinical trial stratified by age and clinics (Mulago or Nsambya) to determine if the availability to see continuous glucose levels by Freestyle Libre 2 CGM will improve glucose TIR compared to SMBG 3x/day. All subjects will receive intensive monthly diabetes self-management education. Half of the subjects (*n* = 90, “CGM Group”) will be given unblinded FreeStyle Libre 2 CGM for the entire 12 months. Half of the subjects (*n* = 90, “Control Group”) will be given sufficient test strips for 3x daily SMBG levels months 1–6. They will wear blinded CGM for endpoint assessment. For months 7–12 they will switch to unblinded CGM.

Primary endpoint assessment occurs after six months of unblinded CGM (months 1–6 for the CGM Group, and 6–12 for the Control Group). The first six months of the Control Group will serve as the control. The CGM Group will receive an additional six months (months 7–12) of unblinded CGM to determine the effects of longer use of CGM wear.

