### 2.6. Study Management

Both study groups receive intensive monthly diabetes self-management education, with a focus on pattern recognition and insulin adjustment to prevent hypo- and hyperglycemia. Between visits, they have unlimited availability to contact study personnel by telephone at all times. Participants return used sensors at each visit. All study procedures are performed by trained personnel. CGM is considered a low-risk medical intervention.

Participants wearing the unblinded FreeStyle Libre 2 CGM system are able to see their glucose levels at all times. The research team is able to use these data for insulin adjustment, and participants are taught how to interpret the data. Subjects in the control arm wear the blinded CGM Libre Pro while performing SMBG three times daily for six months. Patients are taught how to interpret SMBG data and the research team uses these data for insulin adjustment. Blinded FreeStyle Libre Pro CGM sensors, placed monthly, are used to provide control data. The study team uploads the de-identified data to a study website and neither participants nor the research teams have access to the blinded sensor data for clinical use until the end of months 0–6, to preserve the blinding.

Participants are prescribed insulin regimens as per the patient’s usual routine. This was generally human NPH and regular insulin. However, analog insulin, longacting Basaglar and Levemir and rapid novorapid are increasingly becoming widely available. No participants in the study will be on premixed insulin. The insulin pens are stored at room temperature for the majority of the participants.

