### 2.7. Sample Size Determination

The sample size is determined based on hypothesis testing of the primary efficacy endpoint. The null hypothesis is that the two arms will demonstrate no significant differences in the six-month change in glucose TIR. The alternative hypothesis is that wearing unblinded CGM will have greater improvement in glucose TIR over six months compared to the control arm. We estimate a standard deviation of 16.6% for baseline TIR based on our pilot data [3] and assume a moderate correlation of 0.5 between baseline and 6-month TIR values. A sample size of 144 patients (72 per arm) will have over 90% power to detect a difference of 8.6% in 6-month TIR changes between the two arms at the one-sided significance level of 0.05. To allow a 20% dropout rate, a total of 180 patients will be randomized with planned study completion of at least 144 patients. The sample size will have over 90% power to detect a 5-percentage point difference in the 6-month change from baseline in percent time < 70 mg/dL (3.9 mmol/L) or a 3.5 percentage point difference in percent time < 54 mg/dL (3.0 mmol/L) at the one-sided significance level of 0.05.

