### 2.8. Statistical Methods

#### 2.8.1. Primary Efficacy Endpoint

The primary efficacy endpoint is the six-month change in percent TIR. A mixed effects model will be used, with a subject-level random intercept, with the fixed-effect predictors including the time of measurement (0, 6, or 12 month), time-dependent binary indicator for the type of CGM (SMBG with blinded CGM or unblinded CGM), and time-by-CGM-type interaction. Covariates such as age and gender will also included if tested as significant in univariate analysis.

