#### 2.8.2. Cost Analyses

Primary cost analysis: material cost of the Libre CGM system vs. SMBG

We calculated the cost of three times daily SMBG per patient per 1 year. Assumptions to consider included provision of one glucometer per patient per year plus a replacement in up to 20% of patients in the second half of the year, batteries for the glucometer every 6 months, 3 test strips per day per patient plus 10% for supplementing those who might need additional support (such as during acute illness), 1 lancet device per patient per year with replacement of up to 50% in the second half of the year, and two packets of 200 lancets per patient per year. We also calculated the cost of SMBG six times daily per patient per 1 year, since international consensus standards state that SMBG should occur 6–10 times per day for optimum care.

We calculated the direct cost of the Freestyle Libre 2 CGM system per patient per 1 year. This model includes provision of 1 Freestyle Libre 2 CGM reader per patient including rechargeable batteries, 26 sensors per year (one every 14 days), glucose test strips for confirmation of readings four times per week (the CGM system has glucose monitoring capacity, so no separate meter is necessary), one lancet device, and 50 lancets. We assume 10% extra of these supplies for replacement or increased needs, except for sensors, where we assume 20% extra are needed.

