## Figures and Tables

**Figure 1 mps-09-00043-f001:**
[figure not shown]
Study flow diagram figure legend. Dark green color is librepro wear for 2wks, yellow is unblinded CGM wear, blue is for Blinded CGM wear.

**Table 1 mps-09-00043-t001:** Overview of patient schedule activities.

Time (−1 Week, then Monthly)	−1 wk	0	1	2	3	4	5	6	7	8	9	10	11	12
Visit Number	1	2	3	4	5	6	7	8	9	10	11	12	13	14
**Informed Consent/Assent**	X													
**Initial Eligibility Screening, including wearing a single blinded Libre Pro CGM for at least 7 days**	X													
**Final Eligibility, Randomization**		X												
**Complete Medical History**	X													
**Interim Medical History**		X	X	X	X	X	X	X	X	X	X	X	X	X
**Complete Physical Exam**	X													
**Limited/Directed Physical Exam ***		X	X	X	X	X	X	X	X	X	X	X	X	X
**Physical Activity History**		X	X	X	X	X	X	X	X	X	X	X	X	X
**Pregnancy inquiry (as appropriate)**	X	X	X	X	X	X	X	X	X	X	X	X	X	X
**Prior/Concomitant Meds**	X	X	X	X	X	X	X	X	X	X	X	X	X	X
**Adverse Event Assessments**	X	X	X	X	X	X	X	X	X	X	X	X	X	X
**Daily Insulin U/kg/day, Type of Insulin**	X	X	X	X	X	X	X	X	X	X	X	X	X	X
**Severe Hypoglycemia History**	X	X	X	X	X	X	X	X	X	X	X	X	X	X
**Clinic POC HbA1c**	X				X			X			X			X
**Control Group Months 0–6: Libre Pro (blinded) CGM placed in clinic and returned to clinic the following month, test strips dispensed in clinic and SMBG downloaded monthly ****		X	X	X	X	X	X							
**CGM Group Months 0–12 and Control Group Months 7–12: Libre 2 (unblinded) CGMs dispensed in clinic monthly, worn continuously, and completed CGMs returned monthly to clinic**		X	X	X	X	X	X	X	X	X	X	X	X	
**Insulin Dispensed**		X	X	X	X	X	X	X	X	X	X	X	X	X
**Validated Questionnaires *****	X							X						X
**Patient Education**	X	X	X	X	X	X	X	X	X	X	X	X	X	X

* monthly physical exam, ** done monthly for 6 months, *** Questionnaire filled every 6 months.

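### The analysis window in section 2.3 cannot be applied to the control arm, whose single monthly blinded sensor goes on at the visit and is unlikely to last into the following two weeks

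*Protocol article*

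**What the plan says.** Section 2.3 fixes the measurement window for both arms. The data used are those "obtained in the two weeks preceding each monthly visit; thus, the CGM data comparison period will be the same for both groups".

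The control arm's device schedule is in Table 1 and section 2.6:

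- Table 1, months 0-6: "Libre Pro (blinded) CGM placed in clinic and returned to clinic the following month". The row is marked at months 0, 1, 2, 3, 4 and 5.
- Section 2.6: "Blinded FreeStyle Libre Pro CGM sensors, placed monthly, are used to provide control data".
- The Figure 1 legend gives a wear time: "Dark green color is librepro wear for 2wks". It lists blinded CGM wear under a separate colour, with no duration.

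For the CGM arm, and for controls after the switch, Table 1 has "Libre 2 (unblinded) CGMs dispensed in clinic monthly, worn continuously, and completed CGMs returned monthly to clinic", marked at months 0 to 11.

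Section 2.8.1 states: "The primary efficacy endpoint is the six-month change in percent TIR". The mixed model there uses months 0, 6 and 12.

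**The concern.** A sensor applied at a visit records forward from that visit. The section 2.3 window runs backward from the next one. If the sensor stops after about two weeks and visits are about a month apart, the two periods do not meet. The document does not provide for a mid-month placement, application at home or a second blinded sensor in the month. Nor can a later sensor supply month 6 for controls: the last Libre Pro goes on at month 5, and they then move to unblinded CGM.

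The window matters because each visit carries education, and the team uses glucose data to adjust insulin (section 2.6). The Discussion allows that education and attention alone might improve TIR as much as CGM does. If TIR differs between the weeks just after a visit and the weeks just before the next, unequal windows would add that difference to the treatment effect. Randomization would not remove it, because at month 6 the window position would coincide with the CGM-type indicator in the model. Baseline would not cancel it, because both arms share the same pre-randomization Libre Pro wear.

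**Working it through.** **Inputs.** Window: the 14 days before a visit (section 2.3). Control sensor: one per visit, placed at the visit (Table 1, section 2.6). Wear: two weeks, inferred from the Figure 1 legend. For comparison, the baseline wear is at least 7 days (Table 1), and the cost section assumes "26 sensors per year (one every 14 days") for Libre 2, which is the other device. For precision, section 2.7 states: "We estimate a standard deviation of 16.6% for baseline TIR based on our pilot data". It also gives a correlation of 0.5, 72 per arm, a difference of 8.6 points and one-sided 0.05.

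**Step 1: the plan's own power figure.** SD of change = 16.6 × √(2 × (1 − 0.5)) = 16.6. SE of the difference = 16.6 × √(2/72) = 2.77. Power = Φ(8.6/2.77 − 1.645) = 92.8%, which agrees with the stated figure of over 90%. Allowing for dropout, 144/0.8 = 180, also as stated. The sample size does not depend on this point.

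**Step 2: overlap.** With wear w and T days between visits, the sensor covers days 0 to w and the window covers days T − 14 to T. Overlap = max(0, min(w, T) − max(0, T − 14)). For w = 14:

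| Days between visits | Stated window (days) | Overlap (days) |
|---|---|---|
| 21 | 7-21 | 7 |
| 24 | 10-24 | 4 |
| 26 | 12-26 | 2 |
| 28 | 14-28 | 0 |
| 30 | 16-30 | 0 |
| 31 | 17-31 | 0 |
| 35 | 21-35 | 0 |

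Wear of 7 or 10 days also gives 0 at every interval of 24 days or more. At T = 30 the sensor would have to run beyond day 16 to give any overlap, and to day 30 to fill the window.

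**Step 3: month 6.** The control value comes from the sensor placed at month 5, so it covers about months 5.0-5.5. The section 2.3 window applied to the CGM arm covers about months 5.5-6.0. For 14-day wear the midpoints lie T − 14 days apart: 14 days at T = 28 and 16 at T = 30.

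**Step 4: what an offset would do.** The documents give no within-month change in TIR, so the offset b is purely an assumption. Type I error if it favours CGM = Φ(b/2.77 − 1.645). Power if it works against CGM = Φ((8.6 − b)/2.77 − 1.645).

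| Assumed offset b (points) | One-sided type I error, favouring CGM | Power, against CGM |
|---|---|---|
| 0 | 5.0% | 92.8% |
| 1 | 10.0% | 86.5% |
| 2 | 17.8% | 77.1% |
| 3 | 28.8% | 64.8% |
| 4 | 42.1% | 50.7% |

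**The case against.** The two-week wear is not stated for the monthly control sensors. It comes from the legend of a figure that is not shown, and the dark green entry may describe only the baseline wear. This lowers the certainty but hardly changes the result, since shorter wear also misses the window and only wear well beyond two weeks would reach it.

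The stated intention in section 2.3 is equal periods. A reader might infer that the two arms' TIR is in fact measured in different halves of the month. The documents do not support that: it follows only if analysts keep the section 2.3 window for the CGM arm and use another, unstated window for controls. Because Libre 2 is worn continuously, matched windows can be achieved.

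A reader might also infer a bias of a definite size. The documents give no figure, zero is not excluded, and the direction is unknown. Both arms can telephone the study team at any time between visits, which may weaken any visit-linked pattern.

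The article condenses a fuller protocol, which may set out sensor timing. That would explain an omission. It does not remove a contradiction between a rule the article states and the schedule it prints.

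Finally, two cohorts are complete and treatment is open-label, so changing a primary-endpoint window now needs care. This objection stands and shapes the fix.

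**Conclusion.** The point holds as an internal contradiction about the primary endpoint. Section 2.3 states a window, and a claim that it is the same in both arms, which the control arm's sensor schedule does not deliver. With one sensor per visit, wear of two weeks or less and visits 28 to 31 days apart, overlap is 0 of 14 days. Visits closer than 28 days would give partial overlap.

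The consequence is conditional. If the arms were analysed on different windows, any half-month difference in TIR would enter the primary comparison in full. An assumed 0 to 4 points is 0% to 47% of the planned 8.6 (4/8.6 = 0.47). The documents do not show that such a difference exists. Baseline and the sample-size calculation are unaffected.

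**What to change.** Document, before anyone sees comparison data, one post-baseline window counted from the preceding visit that both arms' sensors cover. An example for the six-month value is the first 14 days after the month-5 visit.

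- Correct the sentence in section 2.3 and reconcile it with Table 1 and section 2.6, stating how long the monthly Libre Pro is worn.
- State the month-12 window by the same rule (here, the first 14 days after the month-11 visit), so that all post-baseline values in the model are defined alike.
- Report the CGM arm's last 14 days before the visit as a sensitivity analysis.
- Record the change as a dated amendment. Section 2.3 says investigators are blinded to the comparison until completion, so this can still be done without knowledge of results.

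The cost is small. No new data collection is needed, provided the continuously worn Libre 2 sensors yielded data in that window; this is expected from the schedule, but the article does not report completeness. The downside is that the six-month endpoint is effectively measured at about 5-5.5 months, which the control sensor schedule already imposes. Moving sensor placement to mid-month would not help the cohorts already completed.
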